### Statistical considerations

There is no consensus on how many factors can be included in a factorial survey [33]. Beck and Opp [33] conclude that subjects don't have any difficulties with vignettes up to 6 dimensions, whereas Taylor [23] points out that more than twenty are possible. Nevertheless, most of the studies on factorial surveys have not used more than 8 factors [29,30,33]. Considering the capacity of the human's working memory, having difficulties to capture more than 6 to 9 information units at the same time [37], it makes sense to limit the number of factors included in the vignettes. Therefore, in our main study we will include only the 7 factors mentioned above.

Each participant will receive 11 vignettes for rating. Generally speaking, the number of vignettes for each participant depends on the time available, on the difficulty and complexity of the vignettes and on statistical considerations [33]. Previous studies used various numbers of vignettes given to each subject, ranging from only 3 [30] up to 40 [38] and even more in older investigations [39]. Beck and Opp [33] suggest that when there is no antecedent survey of a specific issue and therefore no information on how many vignettes could be tolerated, a number of 10 to 20 vignettes is reasonable. Furthermore, the number of vignettes should be higher than the number of factors and 10 vignettes seems to be the statistically best solution ([name], University of Duisburg-Essen, personal communication). Under these considerations and due to the complexity of our seven-factor survey, 11 vignettes per participant seem a reasonable choice to us. However, the ideal number of vignettes given to each subject is an additional aspect that will be tested in the pretest.

The vignettes that will be included in the study will be randomly chosen from all possible vignettes. For vignettes selection, two statistical methods are mentioned in the literature [40]. "Random designs" randomly select the desired number of vignettes from all possible vignettes. The disadvantage of this method is that main and interaction effects are confounded in the statistical analysis [22]. In "quota design" a planned selection of the vignettes is suggested to reduce this source of error. Unfortunately, quota designs in complex survey studies including many factors and different numbers of factor levels are computationally demanding and reliable statistical solutions are not available. Furthermore, quota designs are not applicable, if factor combinations have to be excluded from the study for logical reasons like in our design [40]. We therefore chose the random selection method.

Supported by a computer program 40 sets of vignettes will be randomly drawn with replacement from the pool of possible vignettes. The number of 40 results form a calculation based on the total number of vignettes, the expected sample size and the number of vignettes that will be given to each participant [33]. All 40 sets will be available for all three study groups (see "Participants"). Distribution will be at random within groups.

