### Creating vignettes

The principle of a factorial survey is to combine all levels of one factor with all levels of the other factors. Therefore, for writing a vignette, one level of a factor is randomly combined with one level of all other factors, resulting in a description of a specific situation.

Given 7 factors with 2 to 3 levels in our study, we get 432 possible vignettes by 3 × 2 × 2 × 2 × 3 × 3 × 2. Before constructing the vignettes, unrealistic combinations have to be eliminated [33]. Thus, we had to exclude the combination of "prevention" and "direct negative consequences" as there are no prevention procedures with direct negative effects in case of omission. In addition, we had to exclude vignettes containing the combination of "one therapeutic option" with either "treatments are partly well tolerated, may partly have severe adverse effects"or "good evidence for one/some treatment option/s, no evidence for other treatment option/s". Table 2 shows a possible vignette of our study.

**Table 2 T2:** Example of a survey vignette

A patient consults his/her physician because of a mild disease that doesn't affect him right now but could lead to negative consequences in the future. There is no time pressure for beginning the treatment. There are various therapeutic options. Treatments are partly well tolerated and may partly have severe adverse effects. There is good evidence for all therapies. The patient in general wishes to participate in medical decisions.

By considering vignettes in such an abstract manner, we wondered whether all patients could imagine such situations without further details. Therefore we considered constructing vignettes with specific diseases and therapeutic options. To avoid confusion with too much detail we decided to present a semi-concrete solution as shown in table 3.

**Table 3 T3:** Example of a semi-concrete vignette

A patient consults his doctor because of mild elevated blood pressure that doesn't affect him right now but could lead to negative consequences in the future. There is no time pressure for beginning the treatment. The available therapeutic options are: a pill that could have adverse effects or a change of lifestyle that is well tolerated. There is good evidence for all therapeutic options. The patient in general wishes to participate in medical decisions.

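### Excluding vignette combinations does not rule out a planned selection; the random draw with replacement costs modest, avoidable precision, mainly on interactions

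*Protocol article*

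**What the plan says.** Under Creating vignettes, the article crosses seven factors and arrives at the full factorial: "we get 432 possible vignettes by 3 × 2 × 2 × 2 × 3 × 3 × 2". It then removes prevention paired with immediate negative consequences. It also removes a single therapeutic option paired with mixed tolerability or with mixed evidence.

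Under Statistical considerations, it says of random designs that "main and interaction effects are confounded in the statistical analysis". It describes the alternative in broad terms: "In 'quota design' a planned selection of the vignettes is suggested to reduce this source of error". It rejects that alternative on two grounds. The first is heavy computation without reliable solutions when there are many factors with unequal numbers of levels. The second is that "quota designs are not applicable, if factor combinations have to be excluded from the study for logical reasons like in our design". It therefore selects at random: "40 sets of vignettes will be randomly drawn with replacement from the pool of possible vignettes". The set size is fixed in the same section: "Each participant will receive 11 vignettes for rating". All three study groups share the same 40 sets.

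Under Data analysis, mixed models are to estimate the effects of factors and their interactions. Under Participants, the article says that no ICC estimate is available.

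**The concern.** The article names a weakness of its own selection method, names a remedy, and sets the remedy aside on grounds that do not hold for a planned selection as it describes one. A search algorithm needs only a list of admissible vignettes; excluded combinations are simply left off the list.

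What is at stake is precision on the stated aim, the importance of each factor and of interactions between factors. Ratings are clustered in respondents, so a good design balances the levels within each set of 11 as well as over all 440 places. A random draw does neither deliberately. Because the same 40 sets serve every group, an unlucky draw is repeated in all three, and more respondents per set do not remove the imbalance.

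**Working it through.** **The plan's own sample size.** Inputs from Participants: effect size f = 0.25, power 0.95, fixed-effects ANOVA. Assumed: alpha 0.05, 2 numerator df. With noncentrality f²N and denominator df N − 432, the smallest N reaching 0.95 is 438, as stated. 438/11 = 39.8, hence 40 subjects. The plan then takes 100 per group, or 100 × 11 = 1,100 ratings.

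**Admissible pool.** Reason by time of consequences: 3 × 2 − 1 = 5 cells. Options by tolerability by evidence: 2 × 2 = 4 cells with one option plus 3 × 3 = 9 with several, giving 13. The other two factors contribute 2 × 2. Pool: 5 × 13 × 4 = 260 of 432.

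**Estimable terms.** Main-effect dummies: 2+1+1+1+2+2+1 = 10. Two-way products: (10² − (4+1+1+1+4+4+1))/2 = (100 − 16)/2 = 42. The exclusions remove three of them, leaving 39.

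**Feasibility.** A D-optimal exchange search for 40 sets of 11 over the 260 vignettes, with the set as block, finishes in seconds. All 10 + 39 terms are identified.

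**Comparison.** With a random intercept and ICC ρ, a set with design rows x and row total t contributes, up to a constant common to all designs,

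Σ x xᵀ − (c/11) t tᵀ, with c = 11ρ/(1 + 10ρ).

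For ρ = 0.1, 0.3 and 0.5, c = 0.55, 0.825 and 0.917. Sets are assumed to be used equally often. Each coefficient's variance under 200 random draws was divided by its variance under one searched design (target: main effects plus two-way terms) and averaged. The equal-use alternative fills the 440 places with every vignette once and 180 of them twice, allocated to sets at random.

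| ICC | Main-effects model, draw with replacement | Two-way model, draw with replacement | Two-way model, equal use |
|---|---|---|---|
| 0.1 | +6% | +17 to 18% | +5 to 6% |
| 0.3 | +8% | +20 to 21% | +8% |
| 0.5 | +8 to 9% | +21 to 22% | +9 to 10% |

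Where a cell shows a range, repeat searches differed by about a point. Rounded overall: 6–9%, 17–21% and 5–9%. At ICC 0 the first two are about +3% and +13 to 14%. At ICC 0.3 the draw's D-efficiency is 94% (main effects) and 89% (two-way).

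**Other scales.** Standard errors: √1.06 = 1.03 to √1.09 = 1.04 for main effects; √1.17 = 1.08 to √1.21 = 1.10 for the two-way model. Precision lost in the two-way model: 1 − 1/1.17 = 15% to 1 − 1/1.21 = 17%.

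**Source of the two-way loss.** At ICC 0.3, equal use takes it from 20% to 8%, so (20 − 8)/20 = 60% comes from uneven use. The expected number of distinct vignettes in 440 draws with replacement is 260 × (1 − (259/260)⁴⁴⁰) = 212, so about 48 never appear. If replacement means only between sets, with no repeats within a set, the interaction loss hardly changes (19.7% against 20.8% at ICC 0.3).

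**Identifiability.** Every random draw checked had full rank (50, including the intercept).

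**The case against.** The article cites a source for its statement. If that source, which is not shown, reserves the term quota design for exactly balanced or orthogonal fractions, the statement may be true in that narrow sense. This stands as a reason to narrow the sentence rather than call it false without qualification. It does not rescue the choice, since the article describes the alternative broadly and then rejects it.

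The practical effect is modest. With 1,100 ratings per group, dividing by 1.2 or even 1.5 leaves simple F-test power for f = 0.25 above 0.999. It matters only for much smaller effects: at f = 0.10 with 2 df, power falls from 0.85 to 0.78 at an inflation of 1.2. This stands too, although the article already assigns the margin above 40 subjects to the unknown ICC, drop-outs and missing data.

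The trade-off was disclosed, and the article does not limit interactions to two-way terms. That is fair: the 49-term target is a reviewer's choice.

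Three stronger readings are tempting and unsupported:

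- **Confounding means inseparable effects.** The estimable terms remain identified; what remains is avoidable correlation between estimates.
- **The draw gives up 10% of precision on main effects and 20% on interactions.** A main-effect figure near 10% (11% more variance at ICC 0.3) arises only against a design searched for main effects alone, not the one recommended here. Twenty per cent more variance is about 17% less precision.
- **The whole loss follows from rejecting planned designs.** More than half of the two-way loss follows from uneven use of the vignettes, which a random method could also avoid.

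About 22% of random sets lack some factor level; 0.8¹¹ = 8.6% have no prevention vignette. Both effects are already inside the variance ratios and should not be counted again.

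**Conclusion.** The concern holds as a minor to moderate point of efficiency. Neither ground for rejecting a planned selection holds in the article's own sense of the term: a suitable design exists on the 260 admissible vignettes and is found quickly. Against that single design, the planned draw has about 6–9% more variance in the main-effects model and 17–21% more in the two-way model. These figures assume an ICC of 0.1 to 0.5, a random-intercept model, equally used sets, and a target of main effects plus estimable two-way terms. An ICC near zero would shrink the main-effect loss to about 3%, but the article itself rejects independence of judgements. The documents do not support a claim that the study is underpowered for its stated effect size or that effects cannot be estimated.

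**What to change.** 1. Under Statistical considerations, limit the statement on applicability to exactly orthogonal or balanced designs, and drop the remark that reliable solutions are unavailable.
2. Choose the 40 sets of 11 by a D-efficient exchange search over the 260 admissible vignettes. Use the 10 main-effect dummies plus the 39 estimable two-way interactions as target and the set as block. If the pretest changes the number of vignettes per person, rerun the search.
3. At the least, draw without replacement so that the vignettes are used as equally as 440 places allow. This recovers more than half of the two-way loss with no search.
4. Keep the random distribution of sets within the three groups.

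The cost is one design script before the questionnaires are printed, with no extra participants and no change to the planned mixed models. The downside is that the design is tuned to main effects and two-way terms, so higher-order interactions are not specifically protected.

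### The 40 vignette sets are drawn with replacement from a pool of 260 admissible stories that is never counted, so about 46 to 48 stories are never shown and some precision for interactions is lost needlessly

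*Protocol article*

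**What the plan says.** Under Creating vignettes, the protocol article counts the full factorial: "we get 432 possible vignettes by 3 × 2 × 2 × 2 × 3 × 3 × 2". It then removes two kinds of unrealistic story. The first is prevention combined with immediate negative consequences, "as there are no prevention procedures with direct negative effects in case of omission". The second is a single therapeutic option combined with either mixed tolerability or mixed evidence. The number of stories left is not given.

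Under Statistical considerations, "Each participant will receive 11 vignettes for rating", a number still to be tested in the pretest. For the selection, "40 sets of vignettes will be randomly drawn with replacement from the pool of possible vignettes". On the number of sets: "The number of 40 results form a calculation based on the total number of vignettes", together with the expected sample size and the number of stories per person; no formula is shown. All 40 sets are open to all three groups, and "Distribution will be at random within groups".

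The same section concedes that random selection confounds main effects with interactions. It sets quota designs aside as computationally demanding and as inapplicable once combinations have been excluded. Data analysis plans mixed models for factor effects and interactions, and comparisons between the three groups of 100.

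**The concern.** The material shown to participants comes from one draw. Any story missed by that draw is missed for all 300 people, and any accidental association between factor levels is carried by every rating. Recruiting more people multiplies copies of the same 440 places but does not change their composition. Interactions are an explicit aim of the analysis, and they depend most on how evenly the combinations are represented.

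The 440 places exceed the admissible pool by 440 − 260 = 180. Every story could therefore be shown at least once, so replacement gives something up and brings no visible return. A person who meets the same story twice also gives one rating that adds little about the factors.

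**Working it through.** **Inputs.** Factor levels and exclusions: Table 1 and Creating vignettes. Set size 11, 40 sets, drawing rule and hand-out rule: Statistical considerations. Group size 100, effect size 0.25, power 0.95, and 438 observations: Participants.

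**1. Pool.** Full factorial: 3 × 2 × 2 × 2 × 3 × 3 × 2 = 432, as stated.
- Reason × timing of consequences: 3 × 2 = 6, less 1 = 5.
- Options × tolerability × evidence: one option leaves 2 × 2 = 4 and several options leave 3 × 3 = 9, together 13 instead of 18.
- Time pressure: 2. Patient's wish: 2.
- Admissible pool: 5 × 2 × 13 × 2 = 260, confirmed by enumeration.

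**2. Where 40 may come from.**
- 432/11 = 39.3, rounded up to 40.
- 438/11 = 39.8, rounded up to 40.
- 260/11 = 23.6, rounded up to 24.

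The 438 is reproduced by a fixed-effects ANOVA (noncentral F) with f = 0.25, power 0.95, 432 cells, numerator df 2 and alpha 0.05; alpha and df are assumptions. With 260 cells the same calculation gives 283. The match is not unique: 72 cells with 13 df also gives 438.

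**3. Stories never shown.**
- Replacement story by story: 260 × (1 − 1/260)^440 = 47.7 (simulated 95% range 38 to 57).
- Replacement only between sets: 260 × (1 − 11/260)^40 = 46.1.
- Share: 47.7/260 = 18%.
- For comparison, 24 sets drawn story by story (264 places) would miss 260 × (1 − 1/260)^264 = 94.

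**4. Repeats within a set.**
- Story by story: 1 − ∏(1 − i/260), i = 0 to 10, = 0.193. That is 40 × 0.193 = 7.7 sets, or about 300 × 0.193 = 58 participants.
- Between sets only: zero.

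**5. Precision.** D-efficiency relative to equal use of all 260 stories, averaged over simulated draws of 440 places:

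| Model | With replacement | Without replacement |
|---|---|---|
| Main effects | about 99% | 99.9% |
| All estimable two-way interactions | 94.2% (minimum about 91%) | 99.3% |

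**6. Hand-out.** 100/40 = 2.5, so 40 sets cannot be used equally often in a group of 100. Under simple random hand-out:
- Sets unused per group: 40 × (39/40)^100 = 3.2.
- A given set reaches a given group with probability 1 − 3.18/40 = 0.92, so about 40 × 0.92³ = 31 sets reach all three groups.

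**The case against.** The strongest reply is that the study estimates factor effects and interactions, not 260 separate means, and announces from the outset that it uses a random sample of stories. Unseen stories are therefore not a fault in themselves. In 500 simulated draws, main-effect standard errors rose by only about 1.2%, and every two-way interaction estimable in the full pool stayed estimable. The article names the confounding drawback itself and chooses random selection knowingly. All of this stands, and it limits the size of the point. It does not justify replacement: cycling through the whole pool is not a quota design, needs no special algorithm and already respects the exclusions.

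A reader might also infer four stronger things that the document does not support.

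- **That 40 was wrongly sized on 432 and that this causes the gaps.** No formula is given, sample size is named as an input, and other routes also lead to 40. More sets improve coverage: 24 sets drawn in the same way would miss about 94 stories. The gaps come from replacement.
- **That stories certainly repeat within sets.** The wording equally allows replacement between sets only.
- **That the groups rate different sets.** All sets are open to all groups, and about 31 of 40 would be expected to reach all three even with unrestricted hand-out. Random distribution could also be blocked, and story content enters the model.
- **That equal use of the pool would be free of confounding.** The exclusions themselves tie the number of options to tolerability and to evidence. In the pool of 260, the indicators for several options and for mixed tolerability correlate at (3/13 − 9/13 × 3/13) / √(9/13 × 4/13 × 3/13 × 10/13) = 0.37. Only the chance part can be removed.

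**Conclusion.** The point holds as an avoidable inefficiency and a missing count, not as a threat to validity. The pool of 260 follows from the article's own exclusions without any assumption. That about 46 to 48 stories go unshown holds under either reading of replacement; the 19% chance of a repeat within a set holds only if replacement is story by story. The precision loss is about 1% for main effects and about 6% for two-way interactions, and it assumes a D-criterion, equal weight per place and all estimable two-way terms in the model. The link from 40 to 432 is plausible but rests on an assumed alpha and df. Set frequencies will differ between groups at least slightly, because 2.5 uses per set is not a whole number; how much depends on a hand-out rule that the article does not detail.

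**What to change.** - State the admissible pool as 260 after the exclusions, and show how the number of sets is derived from it.
- Draw without replacement: shuffle the pool, use all of it before any story is reused, and allow no repeat within a set.
- Choose a number of sets that divides 100, and use each set equally often within every group. Two examples:
  - 25 sets used four times per group: 275 places, so 245 stories appear once and 15 twice.
  - 100 sets used once per group: 1,100 places = 4 × 260 + 60, so 200 stories appear four times and 60 five times.
- Recalculate these counts if the pretest changes the 11 stories per person.

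The cost is a few lines in the drawing program and a different number of booklet versions: fewer than now with 25 sets, more with 100. No extra participants are needed. The change has to be made before the draw, because the composition of the sets cannot be repaired once ratings have been collected.

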### Participants

To our knowledge there are no well established power analysis methods for hierarchical models in factorial survey study designs. Thus, we decided to use conservative ANOVA for fixed effects, special, main effects and interactions [41]. The sample size was calculated assuming an effect size of 0.25. Defining the single vignette as the unit of analysis, we estimated that a minimum number of 438 observations would be required to detect an effect of 0.25 with a power of 1-β = 0.95. Since one subject has to rate 11 vignettes, 40 subjects would be necessary. As we don't have estimations for intracluster correlation coefficient (ICC) and in order to compensate for drop outs and missing data, we aim at a sample size of 100 persons.

This results in a total number of 300 participants who will be included in the study: 100 general practitioners (GPs), 100 patients and 100 members of self-help groups.

We decided to include GPs because in Germany the general practitioner is the first person in contact with the patient. He is the one who guides the patient through the health care system. Usually, medical treatment is coordinated in a GP's surgery. As a consequence of the special relationship between GP and patient, most important decisions in the medical encounter are made in this context. For the study we will recruit members of our regional GP network as well as attendees of national conferences.

We plan to distinguish between the "usual" patient seen in general practice and members of self-help groups because we expect the latter to be more active in the decision making process. Patients will be recruited in surgeries. Members of self-help groups will also be contacted resorting to self-help group nets.

Patients are included, if they are 18 years and older, able to read German and able to give informed consent. We try to cover different educational levels and age groups, balanced for gender. Patients requiring emergency care are excluded.

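### The stated minimum of 438 observations appears to be sized on all 432 factorial cells, 172 of which the design excludes, so it reflects the cell count more than the assumed effect

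*Protocol article*

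**What the plan says.** Under Participants, the protocol article says that no established power method exists for hierarchical models in this type of survey, and so "we decided to use conservative ANOVA for fixed effects, special, main effects and interactions". The remaining inputs given are "The sample size was calculated assuming an effect size of 0.25", "with a power of 1-β = 0.95", and "Defining the single vignette as the unit of analysis". The result is "a minimum number of 438 observations would be required to detect an effect of 0.25". At 11 ratings per subject this becomes 40 subjects. It is then raised to 100 per group because the intracluster correlation (ICC) is unknown and to cover dropout and missing data. Alpha, numerator degrees of freedom and number of groups are not given.

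Under Creating vignettes, the full factorial is counted: "we get 432 possible vignettes by 3 × 2 × 2 × 2 × 3 × 3 × 2". The same section then says that "unrealistic combinations have to be eliminated" and removes two kinds of combination: prevention with immediate negative consequences, and a single therapeutic option with either of the two mixed levels (for adverse effects or for evidence).

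Under Data analysis, the plan is a mixed model with dummy-coded factors and interactions. Least-squares methods such as ANOVA are rejected there because they assume independent judgements.

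**The concern.** The printed minimum is only 6 more than the number of cells in the full factorial. In an ANOVA power calculation that fits every cell, the error degrees of freedom are N minus the number of cells, so N cannot fall below the cell count whatever the effect size. If 438 arose in this way, it describes a model that the design rules out and that the analysis section does not plan.

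The figure is the base for the 40 subjects. The step from 40 to 100 is the only stated allowance for ICC, dropout and missing data, so a wrong base misstates that allowance. The method is also named for both main effects and interactions at a single power of 0.95, although the two need different numbers.

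**Working it through.** **Inputs.** From Participants: f = 0.25, power 0.95, the rating as unit, 11 ratings per subject, 100 persons per group. From Creating vignettes: 432 cells and the exclusions. Assumed: alpha = 0.05; numerator df (df1) = 2, the main effect of a 3-level factor; 432 groups.

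**Formula.** Power = P(F > critical value), where F is noncentral with df1, df2 = N − groups and noncentrality λ = f²N. The required N is the smallest giving power of at least 0.95.

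**1. Reproducing 438.** With 432 groups and df1 = 2:
- N = 437: df2 = 5, λ = 0.0625 × 437 = 27.31, power 0.923.
- N = 438: df2 = 6, λ = 0.0625 × 438 = 27.38, power 0.951.

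The match is exact, and 438/11 = 39.8 rounds up to the stated 40 subjects.

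**2. How firm is this origin?** Other pairs also return 438 at alpha 0.05, with at least one at every df1 from 2 to 13, for example df1 = 3 with 429 groups or df1 = 12 with 248 to 256. A single effect in this design has df equal to a power of 2. Restricted to those, and to at most 432 groups, the hits are (2, 432), (4, 425), (8, 396) and (8, 397). Only 432 is a cell count in the document. At 432 groups, alpha 0.025 with df1 = 1 and alpha 0.10 with df1 = 3 also give 438, again with 6 error df.

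**3. Cells that exist.**
- Prevention with immediate consequences: 1 × 1 × 2 × 2 × 3 × 3 × 2 = 72.
- One option with at least one mixed level: 3 × 2 × 2 × 1 × (9 − 4) × 2 = 120.
- Overlap: 1 × 1 × 2 × 1 × 5 × 2 = 20.
- Excluded: 72 + 120 − 20 = 172. Feasible: 432 − 172 = 260.

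**4. Models the design can support.** Main effects need 1 + (2 + 1 + 1 + 1 + 2 + 2 + 1) = 11 parameters. All two-way terms would bring this to 53, of which 50 are estimable on the 260 vignettes. Required N at f = 0.25, alpha 0.05, power 0.95, under independence:

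| Model | 2-df effect | 4-df interaction |
|---|---|---|
| 11 parameters (main effects) | 251 | – |
| 50 parameters (two-way) | 251 | 303 |
| 260 cells, saturated | 283 | 322 |
| 432 cells (not fittable) | 438 | 444 |

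**5. Response to effect size (df1 = 2).** With 432 cells the required N is 438 at f = 0.25, 436 at 0.30 and 435 at 0.40. With 11 parameters it is 251, 175 and 100. At the assumed effect and above, the 432-cell figure hardly moves.

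**6. Power for interactions at N = 438 in the 432-cell calculation.** It is 0.823 for 4 df (a 3 × 3 interaction) and 0.586 for 8 df (a 3 × 3 × 3 interaction). The latter would need 463.

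**7. What the target gives.** 100 × 11 = 1,100 ratings per group. Under independence, at about 95% power, these detect f of about 0.12 (2 df) and 0.13 (4 df). With the usual inflation 1 + (11 − 1) × ICC and no dropout:
- 1,100/438 = 2.51, so ICC up to (2.51 − 1)/10 = 0.15.
- 1,100/251 = 4.38, so ICC up to 0.34.
- 1,100/322 = 3.42, so ICC up to 0.24.

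This inflation is only a rough guide, because the vignette factors vary within subjects.

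**The case against.** The strongest reply is that the article discloses its proxy. It says that no established method was available, names ANOVA as a substitute, calls it conservative and admits that the ICC is unknown. That stands, and the ANOVA-versus-mixed-model mismatch is not the point here. The undisclosed part is the apparent use of cells that the same article removes.

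Also fair: alpha and the software inputs are details that an article may leave to a fuller document. Their absence is not a fault in itself, but it means that the 432-cell origin has to be inferred. A reader might take the exact match as proof. It is not, since other input pairs return 438; it is the only one at alpha 0.05 that combines a real effect of the design with a cell count in the document.

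A reader might infer from the 0.82 and 0.59 that interactions are underpowered. The document does not support this. Those values exist only inside a model that cannot be fitted, and on feasible models 438 exceeds the 303 to 322 needed for 4 df. They show only that the stated 0.95 does not cover main effects and interactions alike in the calculation that reproduces it.

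A reader might also infer that 251 observations, or 23 persons (251/11 = 22.8), is the correct minimum and that enrolment could be cut. It is not: all these figures assume independent ratings, which the Data analysis section rejects, and that section does not fix the order of the interactions.

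**Conclusion.** The point holds as a minor reporting correction. The printed minimum is reproduced exactly by a 432-cell ANOVA with 6 error degrees of freedom, while the design has 260 vignettes and the analysis plans dummy-coded terms in a mixed model. Under independence the figure overstates the 2-df need by 438 − 283 = 155 to 438 − 251 = 187 observations. The reserve in 100 persons per group is therefore understated rather than overstated. No planned test is shown to be underpowered, and enrolment is unaffected.

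The conclusion rests on alpha 0.05, on the inferred df and cell count, and on independence of ratings for every recomputed N. The count of 260 feasible vignettes follows directly from the article.

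**What to change.** Keep 100 persons per group. Replace the 438 observations and 40 subjects with a calculation on the 260 feasible vignettes and the planned model terms, stating alpha, numerator degrees of freedom and number of parameters. Give main effects and interactions separately: under independence, about 251 to 283 observations for a 2-df effect and 303 to 322 for a 4-df interaction. Label these as independence-based lower bounds. Then show, over a range of assumed ICC and dropout, what 1,100 ratings per group deliver, starting from the independence case of f about 0.12 (2 df) and 0.13 (4 df) at about 95% power.

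The cost is a rewrite of a few sentences under Participants and one short calculation. Recruitment, vignettes and analysis do not change.
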